**Figure 3 F3:**
[figure not shown]
Minimal detectable relative risk depending on the number of subjects in the intervention group for different levels of incidence of SARS-CoV-2 infection detected in the general population. With 2,000 subjects in each arm (intervention and control), we have a power of 80% to detect a relative risk of 3–4.4 depending on the level of SARS-CoV-2 incidence.

For incidences in the general population of between 100 and 300 positive tests per week per 100,000 people, the detectable excess risk would be between 4.4 and 3 (respectively) for 2,000 participants in the intervention group and 2,000 participants in the control group (ratio 1:1; Figure 3). We simulated the impact of the clustering effect, considering an increased risk of infection within groups of participants who came together to the event. Considering that the secondary attack rate within those groups would be decreased by 80% by the vaccine protection, we could assume that the intra-cluster correlation would be negligible and that the design effect would be close to 1. With a planned attrition rate of 10% of participants for the primary outcome on D7, we plan to randomize a total of 2,200 participants in the “experimental” arm and 2,200 in the “control” arm.

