### Statistical considerations

#### Sample size computation

In a non-inferiority design, the sample size depends on the probability of the observed event (here a SARS-CoV-2 infection), the power of the study, and a threshold of clinical significance.

To define this threshold, we consider that the exposure of a vaccinated population to the event has to lead to an equal or less number of secondary infections than in a non-exposed unvaccinated population. However, according to the risk/benefit balance and the random assignment, both our control and intervention arms need to be fully vaccinated. Consequently, we need to estimate the level of infection which could have been observed in the control group if it had not been vaccinated. Assuming a vaccine efficacy against infection of 80% would mean that the risk of infection is divided by 5, hence we consider that the incidence observed in the control group could have been multiplied by 5 if the control group was not vaccinated. Consequently, we set the non-inferiority threshold to five times the incidence observed in the control group.

As shown in Figure 3, the additional risk could be detected as a function of incidence and sample size, with 80% power and alpha risk of 5%. We corrected observed incidence rates in the population to account for 38% under-detection and 80% vaccine protective effect, as observed in France in 2020 (28).

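### The stated 80% power does not apply to the five-fold ratio margin: with 1 to 3 expected events per arm, power is about 15% to 55%

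*Protocol article*

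**What the plan says.** All the relevant text is in the protocol article under Statistical considerations, Sample size computation, including the Figure 3 caption.

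- **Margin:** "we set the non-inferiority threshold to five times the incidence observed in the control group". The reasoning given is that 80% vaccine efficacy divides infection risk by five.
- **Incidence range:** "between 100 and 300 positive tests per week per 100,000 people".
- **Corrections to incidence:** "We corrected observed incidence rates in the population to account for 38% under-detection and 80% vaccine protective effect".
- **Power:** "With 2,000 subjects in each arm (intervention and control), we have a power of 80% to detect a relative risk of 3–4.4", repeated in the text as "the detectable excess risk would be between 4.4 and 3 (respectively) for 2,000 participants in the intervention group". Alpha is 5%, with no statement of one-sided or two-sided.
- **Clustering:** the design effect is taken as close to 1.

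The primary endpoint is a positive saliva RT-PCR on day 7. The expected number of positives per arm is not given.

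**The concern.** A weekly incidence of a few per thousand at most, cut to one fifth for vaccination and applied to 2,000 people, yields very few infections. The margin is a multiple of the control incidence, which is itself estimated from those few infections. Its sampling error is therefore large and has to enter the power calculation. A claim of 80% power across the whole incidence range looked too high for that situation.

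If the 80% is wrong, readers will overestimate what the trial can settle. A result that fails to exclude a five-fold risk could be taken as a sign of harm or of a failed hypothesis, when the design had limited ability to exclude it.

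**Working it through.** **Inputs.** Incidence 100 and 300 per 100,000 per week; factor 0.2 for the vaccine effect; the 38% figure; 2,000 evaluable per arm; margin 5; alpha 5%; power 80%; design effect 1. All come from Sample size computation.

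**Step 1. Expected control events.** Treating 38% as the fraction of infections detected:
- 100 per 100,000: p0 = 0.001 / 0.38 × 0.2 = 0.000526; 2,000 × p0 = 1.05 events
- 300 per 100,000: p0 = 0.003 / 0.38 × 0.2 = 0.00158; 2,000 × p0 = 3.16 events

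**Step 2. Reproduce the stated figures.** For non-inferiority on the risk difference, with absolute margin (RR − 1)p0 taken as known, true relative risk 1 and one-sided 5%:

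RR = 1 + (1.645 + 0.842) × √(2 / (n p0))
- 1 + 2.487 × √(2 / 1.053) = 4.43 (stated 4.4)
- 1 + 2.487 × √(2 / 3.158) = 2.98 (stated 3)

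Other constructions tried do not match. One-sided 2.5% gives 4.86 and 3.23. A superiority test has 44% and 55% power at the stated relative risks. A log-ratio non-inferiority formula with margins 4.4 and 3 has 28% and 40% power.

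**Step 3. Power for the stated margin.** H0: RR ≥ 5, true RR = 1, 2,000 per arm, one-sided 5%. Apart from the log-ratio formula, power comes from full enumeration of independent Poisson counts. The exact test conditions on the total number of events N, so that under RR = 5 the experimental count is Binomial(N, 5/6).

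| Method | 100 per 100,000 | 300 per 100,000 | True size |
|---|---|---|---|
| Exact conditional | 15% | 46% | 2.2% and 2.9% |
| Mid-P | 23% | 55% | 3.9% and 4.5% |
| Score | 39% | 65% | about 7% and 6% |
| Log-ratio formula | 32% | 65% | not enumerated |

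At one-sided 2.5% the exact test has 7% and 35%.

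**Step 4. Why power is low.** Under the exact test, one control event and no experimental event gives p = 1/6 = 0.167, which does not reject. Two control events reject only if there is no experimental event: (1/6)² = 0.028, whereas two against one gives 0.074. With no control event, a ratio analysis cannot show non-inferiority. That has probability e^(−1.053) = 35% at the low incidence and e^(−3.158) = 4% at the high one.

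**Step 5. Where 80% would hold.** The exact test needs about 7.2 expected events per arm. The incidence is 7.21 / 2,000 × 0.38 / 0.2 = 0.00685, or about 685 per 100,000 per week, more than twice the top of the planned range.

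**Step 6. The 38% wording.** Under-detection of 38% means 62% detected. Dividing by 0.62 gives 0.65 and 1.94 expected events, and the Step 2 formula gives 5.38 and 3.53. The published 4.4 and 3 need division by 0.38.

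**The case against.** **The figures are not a slip.** They reproduce, so calling this an arithmetic error would be wrong. The objection stands. The fault is that the formula does not match the margin and is used with too few events for a normal approximation.

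**The scale matters.** With a pre-fixed absolute margin of 4p0, enumerated power is about 85% and nearly 100%, though with type I error of about 9% and 7%. A reader might infer that zero control events cap power at 65% whatever the margin; that ceiling belongs to ratio analyses only. The article, however, defines the margin as a multiple of the observed control incidence. Applying five times the observed rate and ignoring its sampling error gives 62% and 85% power, with type I error of about 24% and 23%.

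**The choice of test may lie in the SAP, and the exact test is conservative.** Both are fair. The exact results partly reflect its true size of under 3%. But mid-P, much closer to nominal size here, also falls well short of 80%, and so does the score test despite exceeding 5%. The 65% should not be read as the power of a valid 5% test.

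**The event counts may be too low.** The Discussion reports that positivity in the earlier French concert trial was similar to local 14-day incidence. If a two-week window applied here (an assumption), expected events would double to about 2.1 and 6.3. Power would be 32% (exact) to 42% (mid-P) at the low incidence and 75% to 81% at the high one. This is not the article's planning assumption, which is weekly, but it means one cannot say that the trial will most likely be inconclusive at 300 per 100,000.

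**Limitations are acknowledged.** Strengths and limitations says that power depends on incidence. It does not withdraw the 80% claim for the incidence range to which it is attached.

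**Conclusion.** The 80% power statement is wrong as written for the margin that the article sets. On its own planning inputs, with 1.05 to 3.16 expected events per arm, power to exclude a five-fold ratio at one-sided 5% is about 15% and 46% (exact) or 23% and 55% (mid-P) at the two ends of the incidence range. No ratio test examined reaches 80%.

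This rests on a ratio margin, a true relative risk of 1, one week of incidence, 38% read as the detected fraction, and a design effect of 1. A larger design effect would lower power further.

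The 38% wording is a separate contradiction. A reader might infer from the literal reading that the detectable relative risk (5.4) already exceeds the margin of 5 at the low incidence. The documents do not support that as a finding about the design: the sponsor evidently did not calculate with that factor, and the correct reading depends on a cited source that is not available here.

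**What to change.** - Replace the 80% statement and Figure 3 with exact or simulated power for H0: RR ≥ 5, allowing for sampling error in the control incidence.
- State the expected control events (about 1 to 3).
- State the incidence at which 80% power would hold: for the exact test about 7.2 control events, or roughly 690 per 100,000 per week.
- Reconcile the 38% wording with the factor used, and recompute if the factor changes.
- Say that failure to show non-inferiority at 100 to 300 per 100,000 is inconclusive and is not evidence of increased risk.

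The cost is a short recalculation and revised wording. No extra enrolment is asked for. The stated power becomes less favourable.

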### The vaccine against COVID-19 and its efficacy on the delta variant and its transmission

The approved COVID-19 vaccines have lower effectiveness against mild forms of SARS-CoV-2 infections but remain effective to prevent hospitalizations (13–15). Contrasting results have been published regarding the transmission of SARS-CoV-2 among vaccinated. Evidence of the COVID-19 outbreak in a large, vaccinated population have been reported in Provincetown (USA) (16), which has also shown a superspreading event, while transmission in a healthcare setting occurred in Vietnam (17). However, another study in the USA showed few work-related secondary cases in vaccinated healthcare workers. A recent prospective cohort study in the UK found a modest protective effect on COVID-19 transmission (18): The secondary attack rate (SAR) in household contacts exposed to the delta variant was 25 and 38% in vaccinated and unvaccinated contacts, respectively. SAR among household contacts exposed to fully vaccinated index cases (25%; 95% CI 15–35) was similar to household contacts exposed to unvaccinated index cases (23%; 15–31).

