### Location of the study and event

The 2,200 participants of the experimental group will be randomly assigned to one of the two indoor venues called “La Machine du Moulin Rouge” or “La Bellevilloise.” The reservation group of participants will be assigned to the same venue to respect the randomization by block.

“Machine du Moulin Rouge” is a venue with a surface area of 500 m^2^. It has two bars and two ventilation systems: one at the central bar whose ventilation capacity is 10,627 m^3^/h, and another on the main stage whose capacity is 11,000 m^3^/h (Figure 1). “Bellevilloise” is a venue with a surface area of 450 m^2^ and has only one bar. Its ventilation system operates at 7,500 m^3^/h thanks to two machines located at the dance floor and bar levels (Figure 2).

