#### Analysis of secondary endpoints

Risk factors of SARS-CoV-2 contamination (as defined as positive RT-PCR): we will use multi-level regressions to account for the cluster effect. Variables in the model will include socio-demographic data, size of the reservation group, time spent in the event, and use of transportationBy adherence to the health protocol evaluated by online questionnaire, measure quantity, and length of individual contacts (with and without mask) between participants: This analysis will help to identify the time and location of exposure, to make recommendations during the event. This will also feed agent-based transmission models.Identify superspreading events: every positive result will lead to contact tracing to identify transmission paths.Study adherence to sanitary protocol, to identify a way to improve.

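### The protocol's stated reason does not support a design effect of about 1, so the detectable relative risks of 4.4 and 3 are too favourable, which matters mainly at low incidence

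*Protocol article*

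**What the plan says.** Under Study design, allocation is by reservation group of up to 10 people, so that friends stay together. Under Sample size computation the margin is a relative risk of 5: "we set the non-inferiority threshold to five times the incidence observed in the control group". Population incidence is corrected "to account for 38% under-detection and 80% vaccine protective effect, as observed in France in 2020". For incidences "between 100 and 300 positive tests per week per 100,000 people", 2,000 participants per arm are said to give a detectable relative risk of 4.4 (low end) to 3 (high end) at 80% power and 5% alpha.

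On clustering, the same section says that the effect was simulated. It then reasons that vaccination would lower secondary attack within groups by 80%, so that "we could assume that the intra-cluster correlation would be negligible and that the design effect would be close to 1". The article gives no intra-cluster correlation, mean group size or simulation result. The step from 2,000 to 2,200 per arm is for attrition only.

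The introduction's section on the delta variant cites a UK cohort in which the secondary attack rate in "household contacts exposed to the delta variant was 25 and 38% in vaccinated and unvaccinated contacts, respectively". By vaccination of the index case, the same cohort gave 25% (vaccinated) and 23% (unvaccinated).

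Analysis of the primary endpoint describes a comparison of proportions by intention to treat and names no interval method. Under Analysis of secondary endpoints, the risk-factor analysis states "we will use multi-level regressions to account for the cluster effect".

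**The concern.** Two steps in the argument fail. First, the 80% cut is tied to France in 2020, whereas the trial is presented as a study of delta, and the protocol's own delta figures are 1 - 25/38 = 34% by contact vaccination and no reduction by index vaccination.

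Second, a reduced attack rate does not make the intra-cluster correlation negligible. For a rare binary outcome, that correlation is close to the probability that a group mate is positive given that one member is. Low incidence does not shrink it, and a residual attack rate of several per cent leaves it well above zero.

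At stake is the power statement. If the true design effect is above 1, the effective sample size is smaller than 2,000 per arm, the detectable relative risk is larger than stated, and at low incidence it may lie beyond the margin the trial has set.

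**Working it through.** **Inputs from the protocol.** 2,000 per arm; 80% power; 5% alpha (sidedness not stated); margin 5; incidence 100 and 300 per 100,000 per week; the correction for detection and vaccine effect; delta attack rates 25% and 38%; groups of up to 10.

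**Assumptions.** Household attack rates stand in for friend groups. Groups have equal size m. Each affected group has one index case, who infects each other member independently with probability s.

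**1. Reproducing the stated figures.** The reading of the correction that reproduces them is p0 = incidence / 0.38 x 0.20, which gives 52.6 and 157.9 per 100,000. With a true relative risk of 1, unpooled variance and one-sided 5%:

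Detectable RR = 1 + (1.645 + 0.842) x sqrt(2 p0 (1 - p0) / 2000) / p0

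- Incidence 100: 1 + 3.43 = 4.43 (stated 4.4)
- Incidence 300: 1 + 1.98 = 2.98 (stated 3)

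One-sided 2.5% gives 4.86 and 3.23, which does not match. The published figures therefore carry a design effect (DE) of 1.

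**2. Design effect implied by an attack rate.** With one index case, the chance that a group mate of a positive member is also positive is

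rho = s(2 + (m - 2)s) / (1 + (m - 1)s), and DE = 1 + (m - 1) rho.

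Example: s = 0.38 x 0.2 = 0.076 and m = 5 give rho = 0.076 x 2.228 / 1.304 = 0.130 and DE = 1 + 4 x 0.130 = 1.52.

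**3. Effect on the detectable relative risk**, with the same DE in both arms: RR = 1 + 3.43 x sqrt(DE) at incidence 100, and 1 + 1.98 x sqrt(DE) at incidence 300.

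| Attack rate s | m | DE | RR at 100 | RR at 300 |
|---|---|---|---|---|
| 2% (illustrative low value) | 3 | 1.08 | 4.56 | 3.05 |
| 2% | 5 | 1.15 | 4.68 | 3.12 |
| 2% | 10 | 1.33 | 4.95 | 3.28 |
| 7.6% (protocol's 80% cut granted) | 3 | 1.27 | 4.87 | 3.23 |
| 7.6% | 5 | 1.52 | 5.22 | 3.44 |
| 7.6% | 10 | 2.06 | 5.92 | 3.84 |
| 25% (vaccinated household contacts) | 3 | 1.75 | 5.53 | 3.62 |
| 25% | 5 | 2.38 | 6.28 | 4.05 |
| 25% | 10 | 3.77 | 7.65 | 4.84 |

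A separate simulation, with infection brought in at 0.05–0.16% and one round of within-group spread, gave the same design effects to one decimal.

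**4. Where the margin is passed.** The RR reaches 5 when DE = (4/3.43)² = 1.36 at incidence 100, and (4/1.98)² = 4.1 at incidence 300. Power against the margin at incidence 100 falls from 90% (DE 1) to 76% (DE 1.52) and 65% (DE 2.06). At incidence 300 it is still 97% at DE 2.06.

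**5. If clustering acts only in the experimental arm.** DE 1.52 there averages (1.52 + 1)/2 = 1.26, and the RR at incidence 100 is 1 + 3.43 x sqrt(1.26) = 4.85, inside the margin. DE 2.06 averages 1.53 and gives 5.24, outside it.

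**6. Conditional on an unadjusted primary analysis.** The nominal one-sided 5% error would be 1 - Φ(1.645/sqrt(DE)): about 9% at DE 1.5 and 13% at DE 2.06.

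**The case against.** The household figures are not rates for friends who spend one night out together, and the protocol itself calls the evidence on spread among vaccinated people mixed. Mean group size is unknown, and m = 10 requires every group to be at the maximum. At an attack rate of about 2% the design effect is only 1.1 to 1.3, and the margin holds throughout. The protocol says that clustering was simulated, and the details may be in the full protocol. Control groups are not brought together by the trial, so inflating both arms may overstate the effect. With about 2,000 x 0.000526 = 1.05 to 2,000 x 0.00158 = 3.16 expected events per arm, every normal-approximation figure is rough. All of this stands. It limits how precisely the design effect can be stated, but it does not rescue the printed argument, whose own 80% premise leads to a value above 1.

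Two stronger readings are tempting:

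- **That the trial's confidence intervals will be too narrow.** The design effect is a planning assumption. Interval width depends on the primary analysis, for which the article names no method. Naming a multi-level model for a secondary analysis does not show that the primary one ignores clustering, and neither the full protocol nor the analysis plan is shown.
- **That sharing one of two rooms is the dominant correlation.** The experimental arm is indeed split between two venues ("The 2,200 participants of the experimental group will be randomly assigned to one of the two indoor venues"), and the design-effect argument covers only people who came together. But no figure in the document sizes a room-level correlation, and two rooms cannot estimate one.

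**Conclusion.** The point holds as a flaw in the sample size justification. The 80% premise conflicts with the protocol's own delta figures (34% by contact vaccination, none by index vaccination) and, even if accepted, does not lead to a design effect near 1. The consequence is overstated power: detectable relative risks of about 5.2 and 3.4 at a design effect of 1.5 in both arms, or 5.9 and 3.8 at 2.06, in place of 4.4 and 3. It is material near 100 per 100,000, where an average design effect above about 1.36 passes the margin of 5, and tolerable at 300 per 100,000, where the margin is met up to about 4.1. These sizes rest on household attack rates as a proxy, equal groups, a single index case per affected group and a normal approximation. That the final intervals will be too narrow is not established; the error rates in step 6 apply only if the primary analysis ignores the groups.

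**What to change.** - Replace the statement that the design effect is close to 1 by a range, giving the attack rate and group size behind each value, and say whether clustering is assumed in one arm or both.
- Restate the detectable relative risks and Figure 3 over that range. Enrolment stays as planned.
- State that the primary comparison takes the reservation group as the unit of variance, with a method that works with zero or very few events, for example a cluster-level permutation test. Zero control events has probability of about exp(-1.05) = 35% at incidence 100 and exp(-3.16) = 4% at incidence 300, so a method that needs a finite estimated relative risk would often fail. The method must also be set up against the margin, because a plain permutation test addresses equality only.
- As a descriptive addition, report results by venue with the number of attendees positive on D0.

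The cost is wording and analysis time: reservation group, venue and D0 saliva PCR are already part of the design. The downside is wider intervals than an unadjusted analysis would give, and a less favourable stated power at low incidence.

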#### Analysis of the primary endpoint

The primary endpoint of the current study is positive SARS-CoV-2 proportion in saliva samples 7 days after the event in the experimental group compared to the non-experimental groups. Statistical analyses were performed on an intention-to-treat basis.

#### Analysis of secondary endpoints

Risk factors of SARS-CoV-2 contamination (as defined as positive RT-PCR): we will use multi-level regressions to account for the cluster effect. Variables in the model will include socio-demographic data, size of the reservation group, time spent in the event, and use of transportationBy adherence to the health protocol evaluated by online questionnaire, measure quantity, and length of individual contacts (with and without mask) between participants: This analysis will help to identify the time and location of exposure, to make recommendations during the event. This will also feed agent-based transmission models.Identify superspreading events: every positive result will lead to contact tracing to identify transmission paths.Study adherence to sanitary protocol, to identify a way to improve.

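### The SARS-CoV-2 risk-factor regression carries at least four covariates with no condition on event count, while the plan's own figures imply only about 2 to 6 positives

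*Protocol article*

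**What the plan says.** Under Analysis of secondary endpoints, the protocol article names the outcome (a positive RT-PCR) and the method: "we will use multi-level regressions to account for the cluster effect". It then fixes the covariates: "Variables in the model will include socio-demographic data, size of the reservation group, time spent in the event", and transport. Nothing in the section makes the model depend on how many positives occur, and nothing says whether it covers both arms or attendees only.

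Under Sample size computation, the planning incidence is given as "For incidences in the general population of between 100 and 300 positive tests per week per 100,000 people", adjusted as follows: "We corrected observed incidence rates in the population to account for 38% under-detection and 80% vaccine protective effect". The resulting precision is stated as "the detectable excess risk would be between 4.4 and 3 (respectively) for 2,000 participants in the intervention group", with the same number of controls. The margin is a relative risk of 5: "we set the non-inferiority threshold to five times the incidence observed in the control group". Under Participant timeline, controls are kept out of the event.

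**The concern.** A model with at least four slopes and a group-level random effect needs far more positives than this trial is planned to see. Followed as written, it would give either no estimate or odds ratios with intervals so wide that they say nothing. These results are meant to describe how people become infected, and the same list of analyses aims at recommendations for such events, so a spurious odds ratio could be read as a finding.

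One covariate, time at the event, exists only for people who attended. If controls enter the model, its coefficient could be an arm contrast presented as an effect of exposure duration.

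**Working it through.** **1. Inputs (Sample size computation).** Population incidence is 100 to 300 per 100,000 per week. The correction uses 38% for detection and 80% vaccine protection. There are 2,000 evaluable participants per arm, power is 80% and alpha 5%. Applying the 10% attrition exactly gives 1,980 per arm, which changes nothing below materially.

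**2. Reproducing the plan's own figure.** Take p = incidence / 0.38 × 0.2, which is 52.6 and 157.9 per 100,000. For non-inferiority on the risk difference with a true relative risk (RR) of 1 and one-sided alpha 5%:

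detectable RR = 1 + (1.645 + 0.842) × √(2p(1−p)/2,000) / p

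This gives 4.43 and 2.98, against the stated 4.4 and 3. Two alternatives do not fit: one-sided 2.5% gives 4.86 and 3.23, and reading 38% literally as the undetected share (dividing by 0.62) gives 5.38 and 3.53. The detection-rate reading is therefore an inference from the arithmetic; the article does not state it.

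**3. Expected day-7 positives.** Both arms: 2,000 × p × (1 + RR).

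| Scenario | Incidence 100 | Incidence 300 |
|---|---|---|
| RR = 1, both arms | 2.1 | 6.3 |
| RR = 1, both arms, 38% read literally | 1.3 | 3.9 |
| RR at the detectable value (4.4; 3) | 5.7 | 12.6 |
| RR = 5 (margin) | 6.3 | 19.0 |
| RR = 1, attendees only | 1.05 | 3.16 |

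As an outside check within the article, the earlier French concert trial described in the Discussion had 8 + 3 = 11 positives among 3,917 + 1,947 = 5,864 people. That scales to 11/5,864 × 4,000 = 7.5.

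**4. Events per parameter.** With one slope for each of the four named items, the fewest possible: 2.1/4 = 0.5 and 6.3/4 = 1.6 at RR = 1, and 19.0/4 = 4.7 in the most favourable case. The intercept and the group variance are not counted.

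**5. Does a finite maximum-likelihood (ML) estimate exist?** Separation was tested by linear programming in simulated trials with positives placed at random. There was no random intercept, and each cell used 60 or 100 data sets. Covariate distributions and coding are assumed. The table shows the share with no finite estimate; ranges are repeat runs under different assumptions.

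| Model | 2 positives | 4 positives | 6 positives |
|---|---|---|---|
| Seven slopes, three-level transport | 100% | 65–71% | 36–47% |
| Same, binary transport | 90% | 36% | 8% |
| Five slopes | 75–81% | 30% | 8–10% |
| Five slopes, attendees only | 68% | 22% | 8% |

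The 100% is partly forced, because two positives cannot fill three transport categories. With 10 positives and seven slopes, failure was about 5 to 12%.

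**6. Precision when the estimate exists.** For one balanced binary factor with E events, unadjusted and ignoring clustering, the standard error of the log odds ratio (OR) is 2/√E. The 95% limits are the OR divided and multiplied by exp(1.96 × 2/√E):
- E = 2: factor 16; OR detectable with 80% power about 53.
- E = 6: factor 5; detectable OR about 10.
- E = 19: factor 2.5; detectable OR about 3.6.

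Mutual adjustment can be expected to widen these further.

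**7. Group variance.** Reservation groups hold at most 10 people, so 4,000 evaluable participants form at least 400 groups. Two to six positives across 400 or more groups cannot estimate a between-group variance.

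**8. Time at the event.** With both arms in the model, controls are either coded zero, which confounds the covariate with arm, or missing, which removes the control arm. With attendees only, the covariate is defined but about 1 to 3 positives remain at RR = 1.

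**The case against.** - **Sparse-data rules belong in the analysis plan, and this article condenses a longer protocol.** True, and the absence of a fallback would not by itself be a finding. But the article states a method and a covariate list without condition, and its own planning figures do not support them.
- **The range 2 to 6 is the no-transmission case, whereas risk factors matter mainly if transmission occurs.** This stands, which is why the higher scenarios are shown. At the top incidence and RR = 3, about 13 positives are expected and a finite estimate would usually exist. Even about 19 leaves fewer than 5 per parameter. Only an outbreak outside the planning assumptions would support the full model.
- **A reader might infer that the model will usually have no finite estimate.** The documents do not support that across the planning range. It holds with 2 positives; with 6 it depends heavily on coding, which the article does not give. Nor does the article specify maximum likelihood, and a penalised multi-level fit would be compatible with its wording.
- **A reader might infer that time at the event is wrongly modelled for controls.** The article does not say that controls enter this model, and an attendees-only reading is plausible. That part of the concern is conditional.
- **Positive RT-PCR is not tied to day 7 here.** Counting day-0 positives would add a similarly small number and would mix in infections acquired before the event.
- **The article concedes that power depends on incidence.** It does, but that does not qualify this regression.

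**Conclusion.** The point holds as a defect in a stated secondary analysis. At RR = 1 the plan implies about 2 to 6 positives in both arms (1.3 to 3.9 on the literal reading of 38%), or 0.5 to 1.6 per parameter with the fewest possible covariates. With both arms modelled and covariates assumed, no finite ML estimate exists in most data sets with 2 positives, in roughly 30 to 70% with 4 and in roughly 10 to 50% with 6. Where an estimate exists, it is too imprecise to interpret. Both ways of handling time at the event leave the model unusable at RR = 1, though for different reasons.

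The event counts rest on the detection-rate reading and on 2,000 evaluable per arm; the non-existence rates rest on assumed covariates and are indicative only. The analysis is secondary, so the primary non-inferiority conclusion is untouched.

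**What to change.** Make the SARS-CoV-2 risk-factor analysis conditional on the observed number of positives:
- Below a pre-stated minimum (10 is an example, not a figure from the article), list the cases descriptively. If the event adds no risk, reaching 10 has a Poisson probability of about 11% at the top planning incidence and under 0.01% at the bottom, so this branch is the likely one.
- At or above the minimum, fit Firth-penalised logistic models with one factor at a time, label them exploratory, and state how the reservation group is allowed for. A bootstrap over groups is not dependable with so few events.
- Analyse time at the event among attendees only, and name the analysis set for the other factors.

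The cost is a change of analysis wording, with no effect on recruitment or data collection. The downside is that no mutually adjusted odds ratios are reported when counts are low, but those could not have been interpreted.
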